### 3. STUDY OBJECTIVES

#### 3.1. HYPOTHESIS

We hypothesise that a co-designed Japanese Encephalitis Vaccine Decision Aid (JEVaDA) will reduce decisional conflict regarding JE vaccination compared to usual practice. This reduction in decisional conflict is expected to help users make higher-quality decisions that better align with their values.

We also hypothesise that by facilitating more informed and value-aligned decisions, JEVaDA will increase both the intention to vaccinate (planning to receive the vaccine before travel) and actual vaccine uptake. Additionally, we expect that JEVaDA will enhance knowledge related to JE.

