## 2.7 Secondary outcomes

Secondary outcomes and planned statistical analyses are summarised in Table 3.

**Table 3.** Secondary outcomes: summary of statistical analyses to be performed

| Analysis               | Outcome                                                                       | Groups compared             | Adjusted factors*                                   | Test                |
|------------------------|-------------------------------------------------------------------------------|-----------------------------|-----------------------------------------------------|---------------------|
| Knowledge of JE        | Number of post-intervention correct responses to nine JE knowledge statements | Intervention vs. comparator | Pre-intervention knowledge score, age, sex          | Poisson regression  |
| Intention to vaccinate | Change in participants intention to get vaccinated                            | Intervention vs. comparator | Pre-intervention intent to get vaccinated, age, sex | Logistic regression |
| Uptake of JE vaccine   | Self-reported pre-travel JE vaccine uptake                                    | Intervention vs. comparator | Post-intervention intention to vaccinate, age, sex  | Logistic regression |

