## 2.9 Secondary Outcome 2: Intention to vaccinate

*Null hypothesis:* The online JE vaccine decision aid (JEVaDA) does not lead to a greater increase in participants' intention to get vaccinated before their trip compared to standard online health information among Australian adults planning overseas travel to JE risk areas.

*Research question:* Does use of JEVaDA lead to a greater increase in participants' intention to get vaccinated before their trip compared to standard online health information among Australian adults planning overseas travel to JE risk areas?

Intention to vaccinate will be assessed by the change in response to the question "Do you want to get a JE vaccine before your upcoming trip?". This question will be asked in both the pre-intervention and post-intervention surveys. Response options include: "No, I do not want to", "Yes, I

do want to”, “I am not sure”, and “I am already vaccinated”. For analysis, responses will be recoded into a binary variable, where “Yes, I do want to” is coded as 1, and all other responses are coded as 0. A new binary outcome variable will be created to capture positive change, defined as a shift from 0 pre-intervention to 1 post-intervention.

This outcome will be analysed using multivariable logistic regression. The dependent variable will be whether participants demonstrated a positive change in intention to vaccinate, and the primary independent variable will be group allocation. Baseline (pre-intervention) intention to vaccinate, age and sex will be included as covariates to adjust for baseline differences. Findings will be reported as adjusted odds ratios (ORs) with 95% confidence intervals (CIs) and p-values to indicate the strength and significance of the associations (Table 6).

**Table 6.** Logistic regression analysis of intention to vaccinate

| Variable                                 | Adjusted odds ratio (aOR) | 95% CI | p-value |
|------------------------------------------|---------------------------|--------|---------|
| Intervention group
(reference=JEVaDA) |                           |        |         |
| Baseline intention to
vaccinate       |                           |        |         |
| Age                                      |                           |        |         |
| Female sex                               |                           |        |         |

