### **Secondary Outcome 3: JE vaccine uptake**

*Null hypothesis:* The online JE vaccine decision aid (JEVaDA) does not lead to a greater increase in pre-travel JE vaccine uptake compared to standard online health information (HealthDirect fact sheet) among Australian adults planning overseas travel to JE risk areas.

*Research question:* Does use of JEVaDA lead to a greater increase in pre-travel JE vaccine uptake compared to standard online health information (HealthDirect fact sheet) among Australian adults planning overseas travel to JE risk areas?

JE vaccine uptake will be measured through self-reported responses to the question, "Did you receive a vaccine for Japanese encephalitis before your trip?" in an optional follow-up survey. Responses will be coded as 1 for “Yes” and 0 for “No” or “I don’t remember”.

This outcome will be analysed using multivariable logistic regression. The dependent variable will be self-reported JE vaccine uptake (binary) and the primary independent variable will be group allocation. As intention has been shown to be strongly associated with actual uptake and may confound the relationship between intervention and uptake, post-intervention intention to vaccinate will be included as a covariate, alongside age and sex. Findings will be reported as adjusted odds ratios (aORs) with 95% CIs and p-values (Table 7).

**Table 7.** Logistic regression analysis of JE vaccine uptake

| Variable                                 | Adjusted odds ratio (aOR) | 95% CI | p-value |
|------------------------------------------|---------------------------|--------|---------|
| Intervention group
(reference=JEVaDA) |                           |        |         |
| Post-intervention intention              |                           |        |         |

|              |  |  |  |
|--------------|--|--|--|
| to vaccinate |  |  |  |
| Age          |  |  |  |
| Female sex   |  |  |  |

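### The only uptake model adjusts for post-intervention intention, which the aid is expected to change, so its odds ratio does not answer whether JEVaDA increases JE vaccine uptake

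*Combined protocol and SAP*

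**What the plan says.** The uptake section of the SAP (Secondary Outcome 3) poses a comparison between arms. Its research question begins "Does use of JEVaDA lead to a greater increase in pre-travel JE vaccine uptake compared to standard online health information (HealthDirect fact sheet". The outcome is a yes/no answer in the optional follow-up survey, analysed by logistic regression on group, with this addition: "post-intervention intention to vaccinate will be included as a covariate, alongside age and sex". SAP 2.7, Table 3, lists the same adjustment set, "Post-intervention intention to vaccinate, age, sex", and Table 7 has a row for it.

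Two reasons are given: that "intention has been shown to be strongly associated with actual uptake", and that it "may confound the relationship between intervention and uptake".

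Other parts of the documents bear on this:

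- Protocol 3.1 hypothesises that "JEVaDA will increase both the intention to vaccinate (planning to receive the vaccine before travel) and actual vaccine uptake".
- SAP 2.9 makes intention an outcome in its own right (Secondary Outcome 2) and says of the intention item: "This question will be asked in both the pre-intervention and post-intervention surveys".
- The intention model in SAP 2.9 uses the earlier measurement: "Baseline (pre-intervention) intention to vaccinate, age and sex will be included as covariates to adjust for baseline differences".
- Protocol 5.10 describes no uptake analysis. The SAP gives no uptake model without post-intervention intention and no mediation analysis.

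**The concern.** A confounder of the arm-uptake relation has to influence arm, or share a cause with it. Arm is assigned at random once the pre-intervention survey is complete (protocol 4 and 5.2). Post-intervention intention is recorded after the assigned material has been reviewed, so it cannot have influenced assignment. On the documents' own account it is a mediator: the aid is expected to raise it, and it is said to predict uptake strongly.

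Holding a mediator fixed changes the question. The planned odds ratio compares travellers in the two arms who ended with the same intention, so any gain in uptake that came from changing intention is adjusted away. There is a second problem. If something unmeasured, such as general health-seeking, drives both intention and uptake, then conditioning on intention makes the arms differ on that factor within each intention level, and the remaining estimate is biased.

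The stake is a wrong conclusion on one of the trial's stated hypotheses. An aid that raises uptake mainly by raising intention could be reported as having no effect on uptake.

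**Working it through.** **The plan's figures.** The documents give no uptake rate, intention rate, odds ratio or power for this outcome. The one sample-size figure (SAP 2.5) is for the DCS, and it reproduces: 2 × (1 − 0.5²) × (1.960 + 1.282)² / 0.30² = 175.1 per group, and 350 / 0.70 = 500. I use 175 per arm below only as a convenient size. The uptake set will probably be smaller, because follow-up is optional.

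**Covariates side by side.**

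| Outcome | Prior-state covariate | Measured |
|---|---|---|
| DCS (SAP 2.6) | DCS score | before the intervention |
| Knowledge (SAP 2.8) | knowledge score | before |
| Intention (SAP 2.9) | intention | before |
| Uptake (Secondary Outcome 3) | intention | after |

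Only the uptake model uses a post-randomisation covariate.

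**Illustration.** All rates are assumptions. Let q be the proportion intending in an arm, and u1 and u0 the uptake in intenders and non-intenders. Then uptake in the arm = q·u1 + (1 − q)·u0, and the marginal total OR is the ratio of the two arms' odds. ORs are JEVaDA versus fact sheet; Table 7 names JEVaDA as the reference, so its printed values would be the reciprocals. Age and sex are left out.

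*Full mediation.* Intention 30% vs 45%, u1 = 60%, u0 = 5% in both arms.
- Control: 0.30 × 0.60 + 0.70 × 0.05 = 0.215
- JEVaDA: 0.45 × 0.60 + 0.55 × 0.05 = 0.2975
- Total OR: (0.2975/0.7025) / (0.215/0.785) = 1.55
- Planned model: uptake is equal across arms within each intention level, so the OR is 1.00 by construction.

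*Partial mediation.* Intention 30% vs 50%, u1 = 40%, u0 = 5% in control, plus a direct OR of 1.5 within each intention level.
- Control: 0.30 × 0.40 + 0.70 × 0.05 = 0.155
- JEVaDA intenders: odds 0.667 × 1.5 = 1.0, so 50%. Non-intenders: odds 0.0526 × 1.5 = 0.0789, so 7.3%.
- JEVaDA: 0.50 × 0.50 + 0.50 × 0.073 = 0.287
- Total OR: (0.287/0.713) / (0.155/0.845) = 2.19. The planned model returns 1.50.

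Further cases, from large-sample logistic fits:

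| Assumed case (intention; uptake in non-intenders/intenders) | Uptake, control vs JEVaDA | Marginal total OR | Planned model OR |
|---|---|---|---|
| 30% vs 50%; 5%/40%; no direct effect | 15.5% vs 22.5% | 1.58 | 1.00 |
| 30% vs 45%; 5%/40%; no direct effect | 15.5% vs 20.7% | 1.43 | 1.00 |
| 30% vs 50%; 5%/40%; direct OR 1.25 | 15.5% vs 25.8% | 1.90 | 1.25 |
| 30% vs 30%; 5%/40%; direct OR 1.5 | 15.5% vs 20.1% | 1.37 | 1.50 |
| First row plus shared cause, ±1.0 log-odds | 22.4% vs 28.6% | 1.39 | 0.88 |
| First row plus shared cause, ±1.5 log-odds | 29.0% vs 34.0% | 1.26 | 0.81 |

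In the fourth row the aid does not move intention. The planned OR then exceeds the marginal one only because odds ratios are non-collapsible, so the two columns are not on exactly the same scale. In the last two rows an unmeasured binary factor raises both intention and uptake, there is no direct effect, and the planned model points the wrong way.

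**Rejection rates** (2,000 simulated trials, 175 per arm, two-sided 5%). In the first row, about 40% without post-intervention intention and about 5% with it. In the partial-mediation case with direct OR 1.5, 84% and 28%.

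**The case against.** The strongest objection is to the size. A reader might infer that the adjustment removes the whole effect of the aid on uptake. The documents do not support that, because they nowhere say that intention carries all of it. Protocol 4.1 says the aid prompts users to consult a healthcare provider, which could change uptake after the intention question has been answered. If intention enters in the binary coding of SAP 2.9, a move from refusal to uncertainty is not captured either, and its effect would stay in the group coefficient. Cases with an adjusted OR of exactly 1.00 assume no direct effect. This objection stands, and it limits the claim to the part of the effect that passes through intention.

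Second, randomisation balances the arms as randomised, not necessarily those who take the optional follow-up and are routed to the vaccine question (protocol Appendix 4). Arm imbalance is therefore possible in the analysed set. That is fair, but the SAP's reason is confounding, not selection, and a mediator in the outcome model still fails to give the total effect.

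Third, intention predicts uptake, so adjusting for it may sharpen the estimate. Pre-intervention intention can serve that purpose without lying on the pathway.

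Fourth, uptake is a secondary outcome with no power calculation. That is true and limits the consequences, but uptake is a stated hypothesis and this is its only specified model.

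**Conclusion.** The concern holds in a bounded form. The planned model targets an effect of JEVaDA on uptake with post-intervention intention held fixed, while the SAP's question concerns the total effect. The confounding rationale does not apply to a variable measured after randomisation that the aid is expected to change. The part of the effect running through intention is removed, and what remains may be biased by shared causes of intention and uptake.

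The actual distortion cannot be computed from the documents. On the assumed rates, the planned OR is 1.00 where the marginal total OR is 1.43 to 1.58 under full mediation. It is 1.25 against 1.90, or 1.50 against 2.19, under partial mediation, and 0.81 to 0.88 against 1.26 to 1.39 with a strong shared cause. Complete loss of the effect is a limiting case, not a prediction. The primary DCS analysis and the sample size are not touched.

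**What to change.** In the text of Secondary Outcome 3, in Table 7 and in Table 3, replace post-intervention intention with pre-intervention intention, and keep age and sex as the SAP defines them. Delete the confounding rationale. If the pathway through intention is of interest, report the current model only as a labelled exploratory mediation analysis, stating its assumption of no unmeasured causes shared by intention and uptake.

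The new odds ratio will be conditional on baseline intention, age and sex. It need not equal the marginal ORs above, so report uptake proportions by arm beside it.

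No new data are needed, since the question is already in the pre-intervention survey. The cost is procedural. SAP section 3 describes Version 3 (3 March 2025) as final before data analysis, and Version 3.1 (13 November 2025) as leaving the planned analyses unchanged. The change should therefore be a dated amendment that says whether uptake results were known when it was made. If they were, report both models and identify which was prespecified.

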### Section 3. Changes to the Statistical Analysis Plan

- Version 1 (3-Dec-2024): Included analyses for both intention-to-treat (ITT) and per-protocol populations. Primary outcome analysis specified as ANCOVA with change in DCS score as the dependent variable.
- Version 2 (19-Feb-2025): Revised to use a modified ITT population as the primary analysis set.
- Version 3 (3-Mar-2025): Revised primary outcome analysis to ANCOVA with post-intervention DCS score as the dependent variable, including pre-intervention DCS score as a covariate (rather than modelling change in scores). This approach was adopted to improve statistical efficiency and reduce bias associated with change-score models. This version represents the final SAP prior to data analysis.
- Version 3.1 (13-Nov-2025): Minor editorial changes to align with journal style requirements, including updates to the study title and section headings. No changes to planned analyses.

